### Exit strategy

A careful exit strategy is required due to the vulnerability of the participants, and may be required in the following situations:The situation in which a participant decides to exit the study prematurely. Reasons for this could vary from sickness of the participant to lack of time to participate or even lack of interest in the project, etc.In this case, a questionnaire to explore the reasons for exit will be carried out. During the informed consent process, it will be clearly stated that a participant can leave at any time with no obligation to communicate the reasons for leaving. Therefore, the participant will be invited to voluntarily answer the questions of the exit questionnaireIt will also be made clear to participants that leaving the project does not have any implications for the care that they receive and in a (voluntary) exit interview staff involved in the project will make sure that the project has come to a satisfactory closure and the participant feels comfortable with the situationThe situation in which the study period has come to an end.From the beginning of the pilot, it will be made clear to the participant that the study period is a maximum of 12 months of treatment and an additional 12 months of follow-upFrom the beginning of the study, it will also be clearly explained how the study will come to a close, ensuring participants are aware of the ending strategy and to prepare them for transition and closureIf possible, options to continue using the GRADIOR and/or ehcoBUTLER platform under supervision of a mentor can be discussed (budget and time permitting)After closure of the study, the participant is expected to be able to use the ehcoBUTLER platform on their own. An information letter can be offered to answer the most common questions and to indicate a telephone number in case there are any questions after the study has ended

Neither study coordinators nor other members of staff can control or influence the interventions of participants in the TAU group. Therefore, participants with TAU can participate by their own initiative on other cognitive rehabilitation or stimulation programmes outside the competence of INTRAS Foundation.

## Discussion

We will conduct a RCT with a long-term cognitive rehabilitation intervention and follow-up. This innovative RCT aims to determine the influence of a long-term, computerised, cognitive rehabilitation programme on people with MCI and PwD in comparison to psychosocial stimulation and TAU. The preliminary usability study will focus on ensuring that this type of treatment is more convenient and beneficial for older people, as well as for healthcare professionals.

Limitations of the study are related to the long duration of the treatment along with the 1 year follow-up. Therefore, we expect a large number of participants to drop out due to loss of interest, medical reasons or worsening of a related health condition, changes in life situation, etc. This potential dropout rate has been considered in the sample size calculation to ensure the success of the trial. We also foresee the potential for interviewers and staff to drop out during the study. In this case, every new member of staff recruited will be informed about the study and every new interviewer will undergo the same training in evaluation tools as those recruited at the start of the study.

For ethical and practical reasons, participants in this study will not be blinded to the intervention condition. Huntley et al. [55] recommend conducting single-blinded psychosocial intervention RCTs to minimise other factors, such as socialisation, when using the TAU control group (e.g. patient blinded and assessor blinded, but not therapist blinded). However, this is difficult to apply in practice due to ethical reasons. Therefore, we are conducting a single-blinded RCT with four parallel groups. In this study, all interviewers will be blinded to participants’ treatment allocation. Study coordinators who will manage and adjust the GRADIOR treatments of all participants will do so only based on data obtained from the programme and manage this under a participant’s code (Fig. 1 and Additional file 1).

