## Methods

### Design

This is a multi-centre, randomised controlled, interviewer-blinded trial, with four parallel groups, 1:1:1:1 allocation ratio. Potential participants will be identified by collaborating professionals at recruitment sites and those interested in participating will sign an informed consent form. Subsequently, those selected based on inclusion/exclusion criteria (*n* = 400) will undergo preliminary testing and will be randomly allocated to one of the four study groups. In this study, there are three intervention groups and one group receiving TAU. Intervention groups are: (1) cognitive rehabilitation with the GRADIOR programme (GRA), (2) a computer-based psychosocial stimulation group (ehcoBUTLER) (PSS) and (3) a group receiving a combined treatment of GRADIOR together with computer-based psychosocial stimulation (ehcoBUTLER CARE) (COM). Primary and secondary measures data will be collected at baseline, at 4 months after the start of the treatment and at 12 months, immediately after completing the interventions. Follow-up assessments will be carried out 4 and 12 months after finishing the treatment (months 16 and 24 of the study). A preliminary study of usability will be conducted before the start of the trial. The full study timeline is described in Table 2.

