Carers will also be assessed at the same time as participants, whereby we will evaluate the following: their anxiety using the *State-Trait Anxiety Inventory (STAI)* [51], symptoms of depression with the *Beck Depression Inventory II (BDI-II)* [52], carer overload using the *Caregiver Burden Interview – Zarit Test* [53] and the quality of their relationships using the *Quality of Carer-patient Relationship (QCPR*) *questionnaire* [49]. We anticipate that GRADIOR will positively influence carer-outcome measures, and therefore, we hypothesise that in both intervention groups using GRADIOR, caregiver burden, anxiety and depression will decrease, and the relationship between the carer and the PwD will improve.

The data collected from the InterRAI Home Care Assessment will be used to analyse the cost-effectiveness of the treatment and its impact on health. The economic evaluation will employ a cost-consequences framework evaluating the associated costs and outcomes of the three types of interventions, in comparison to usual care. The evaluation will also assess the main sources of costs associated with the interventions. Primary analysis will be based on the most plausible real-world costs, including the cost of the technology and technical progress. The support costs for GRADIOR and ehcoBUTLER associated with technical aspects of installation, maintenance of hardware and information, as well as communication technology input related to software and data management, will be based on data gathered from sites. This will also include the input of professionals for guiding participants and support provided to participants throughout the intervention. For a complete list of the assessment tests used and the time schedule see Tables 2 and 3 respectively.

**Table 2 Tab2:** Assessments

Activity/assessment	Staff member	Time	Pre-study	Pre-study baseline	2	4	6	8	10	12	16	24
Usability study	Interviewer	N/A	X									
Focus group		90										
SUS		N/A										
Consent Form	Study coordinator	5	X	X		X				X	X	X
Inclusion/exclusion criteria	Study coordinator	N/A	X									
DSM-5 criteria	Interviewer	N/A	X									
Cognitive assessment	Interviewer	106										
MMSE		20		X		X				X	X	X
ADASCog		40		X		X				X	X	X
WAIS III: Calculus		5		X		X				X	X	X
WAIS III: Digit Span		5		X		X				X	X	X
WAIS III: Coding digit symbol		2		X		X				X	X	X
TMT A and B		10		X		X				X	X	X
Semantic and phonologic verbal fluency		4		X		X				X	X	X
CAMCog matrices		5		X		X				X	X	X

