Clock Drawing Test		10		X		X				X	X	X
Pattern recognition test		5		X		X				X	X	X
ADL/iADL (InterRAI HC)	Interviewer	N/A		X		X				X	X	X
Quality of life	Interviewer	20										
EQ5D-5 L		5		X		X				X	X	X
LSNS (Luben)		15		X		X				X	X	X
Mood	Interviewer	15										
GDS		15		X		X				X	X	X
Patient-carer relationship		N/A										
QCPR				X		X				X	X	X
Technological assessment	Interviewer	N/A										
ETUQ				X								
Randomisation	Study coordinator	N/A		X								
Treatment (group-specific)	Study coordinator	N/A			X	X	X	X	X	X		
Termination Form	Study coordinator	N/A	As needed throughout the study									
Adverse Event Form	Study coordinator	N/A	As needed throughout the study									
Progress notes	All	N/A	X	X		X				X		
Communication log	All	N/A	Every phone or in-person contact outside of regular visit									

*ADASCog* Alzheimer’s Disease Assessment Scale – Cognitive Subscale, *ADL* activities of daily living, *CAMCog* Cambridge Cognition Examination, *EQ5d-5 L* EuroQoL 5 dimensions, 5 levels, *ETUQ* Everyday Technology Use Questionnaire, *GDS* Geriatric Depression Scale, *LSNS* Luben Social Network Scale, *MMSE* Mini Mental State Examination, *N*/*A* not applicable, *QCPR* Quality of Patient-carer Relationship, *SUS* System Usability Scale, *TMT* Trail-making test

**Table 3 Tab3:** Time schedule

Activity/month	Responsible	−3	−2	−1	0	1	2	3	4	5	6	7	8	9	10	11	12	13	14	15	16	17	18	19	20	21	22	23	24	25	26	27
Project development	Primary researchers	X	X	X																												
Ethical Committee approval	Primary researchers			X																												
Protocol preparation	Primary researchers	X	X	X																												
Usability study (US)		X	X	X	X	X	X	X	X	X	X	X	X	X	X	X	X	X														
Informed consent for US	Researchers responsible for US			X																												
Participants selection for US	Researchers responsible for US			X																												
*Focus group*	Researchers responsible for US			X																												
Users’ testing	Researchers responsible for US			X																												
Intermediate evaluation	Researchers responsible for US				X	X	X	X	X	X	X	X	X	X	X	X	X															
Incidence registration	Researchers responsible for US																	X														
Randomised controlled trial		X	X	X	X	X	X	X	X	X	X	X	X	X	X	X	X	X	X	X	X	X	X	X	X	X	X	X	X			
Interviewers’ training	Responsible for interviewers		X	X																												

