Participants selection	Responsible for interviewers			X																												
Baseline evaluation	USAL			X																												
Treatment revision	Interviewers			X					X																							
Participants evaluation	Interviewers								X								X				X								X			
Randomisation	USAL/Sacyl/INTRAS			X																												
Intervention implementation	Primary researchers				X	X	X	X	X	X	X	X	X	X	X	X	X	X	X	X	X	X	X	X	X	X	X	X	X			
Data management and results		X	X	X	X	X	X	X	X	X	X	X	X	X	X	X	X	X	X	X	X	X	X	X	X	X	X	X	X	X	X	X
Database development	IBIP + USAL			X	X																											
Data collection	Interviewers				X				X								X				X								X			
Data analysis	Primary researchers + USAL														X	X	X	X	X	X	X	X	X	X	X	X	X	X	X	X	X	X
Data coding and upload	Primary researchers + USAL			X	X				X								X				X								X			
Hypotheses testing	Primary researchers + USAL								X	X	X	X	X	X	X	X	X	X	X	X	X	X	X	X	X	X	X	X	X	X	X	
Results and conclusions	Primary researchers				X	X	X	X	X	X	X	X	X	X	X	X	X	X	X	X	X	X	X	X	X	X	X	X	X	X	X	X
General project evaluation	Primary researchers	X	X	X	X	X	X	X	X	X	X	X	X	X	X	X	X	X	X	X	X	X	X	X	X	X	X	X	X	X	X	X
Dissemination		X	X	X	X	X	X	X	X	X	X	X	X	X	X	X	X	X	X	X	X	X	X	X	X	X	X	X	X	X	X	X
Dissemination of results (publications, conference presentations)	Primary researchers								X	X							X	X	X	X	X	X	X	X	X	X	X	X	X	X	X	X

*IBIP* Iberian Institute of Research in Psychosciences*, Sacyl* Health system in Castile and Leon, *USAL* University of Salamanca

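### Table 3 gives treatment revision to the interviewers who rate the outcomes, which contradicts the stated interviewer blinding and the coordinator roles set out elsewhere

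*Protocol article*

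**What the plan says.** Blinding is stated three times. The Background calls the trial interviewer-blinded. The Design section says "This is a multi-centre, randomised controlled, interviewer-blinded trial, with four parallel groups, 1:1:1:1 allocation ratio". The Discussion says "In this study, all interviewers will be blinded to" each participant's allocation and adds that participants are not blinded.

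Two tables name who does what:

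- Table 2 assigns the cognitive battery, which includes ADASCog, to the interviewer ("Cognitive assessment Interviewer").
- Table 3 has the row "Participants evaluation Interviewers", marked at months 4, 12, 16 and 24.
- Table 3 also has a separate row, "Treatment revision Interviewers", marked at months -1 and 4.

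Elsewhere, treatment belongs to coordinators. Table 2 gives the group-specific treatment row to the study coordinator. The Treatment adherence section describes treatment coordinators trained to set up and adjust GRADIOR treatments. The Discussion says study coordinators manage and adjust GRADIOR under a participant code, using only data from the programme. The section on modifications to the interventions, by contrast, says the 4-month tests also supply data for modifying treatment.

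**The concern.** Participants know their arm, so blinding of the interviewers is the only masking that protects outcome measurement. ADASCog is administered by an interviewer. A person who revises a participant's study treatment learns at least whether there is one to revise and whether it involves GRADIOR. That is the information a rater must not have, since the primary hypothesis compares the two GRADIOR arms with treatment as usual.

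The month-4 revision falls before the 12-month assessment and both follow-up assessments. If interviewers carried it out, detection bias in those ratings could not be excluded, and the description of the trial as interviewer-blinded would not match its own schedule.

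**Working it through.** The protocol gives no figure to reproduce here. The check is a comparison of role assignments.

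| Task | Place | Role | Months |
|---|---|---|---|
| Cognitive assessment incl. ADASCog | Table 2 | Interviewer | Baseline, 4, 12, 16, 24 |
| Participants evaluation | Table 3 | Interviewers | 4, 12, 16, 24 |
| Treatment revision | Table 3 | Interviewers | -1, 4 |
| Group-specific treatment | Table 2 | Study coordinator | 2 to 12 |
| Setting up and adjusting GRADIOR | Treatment adherence | Treatment coordinators | not dated |
| Managing and adjusting GRADIOR | Discussion | Study coordinators | not dated |

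**Step 1: is the revision arm-specific?** Yes. The GRADIOR section says each participant's treatment is adjusted after 4 months, and the combined-treatment section applies the same procedure to that arm. GRADIOR is used only in GRA and COM. In the treatment-as-usual arm the study delivers nothing, and staff may not influence care. Revising treatment therefore separates GRADIOR users from others.

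**Step 2: does it precede the ratings that matter?** The month-4 mark precedes the ratings at 12, 16 and 24 months. The month -1 mark is weaker evidence: Table 3 starts intervention at month 0, so no delivered treatment exists to revise.

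**Step 3: could the row mean only that interviewers test at month 4?** That testing already has its own row under the same role, so the revision row appears to mean something more. The section on modifications leaves room for the milder reading.

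**Step 4: a related mismatch.** The Discussion bases GRADIOR adjustment only on programme data. The section on modifications says the 4-month tests also inform changes. Both cannot hold as worded.

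**Illustration of what rater knowledge could do.** Assume no true effect, a two-sided 5% test of one active arm against control, and a mean rater leniency of *s* SD toward the active arm. The protocol's 340 expected completers over four arms give 340/4 = 85 per arm. The noncentrality is *s* × √(85/2) = 6.519*s*, and the rejection rate is P(Z > 1.960 − 6.519*s*) + P(Z < −1.960 − 6.519*s*).

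| *s* (assumed) | Noncentrality | Rejection rate |
|---|---|---|
| 0.10 | 0.652 | 0.100 |
| 0.15 | 0.978 | 0.165 |
| 0.20 | 1.304 | 0.256 |

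The values of *s* are assumptions; nothing in the protocol supplies one.

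**The case against.** The strongest reply is that the Table 3 row is a mislabel. Three places give treatment adjustment to coordinators and one row of a planning chart differs. Table 3 is coarse elsewhere too: it marks intervention implementation through month 24 under the primary researchers, although treatment lasts 12 months and coordinators manage it. The row may also mean only that interviewers supply the month-4 scores. In addition, the table names a role, not a person, and the scoring training, with its required kappa of 0.80, limits a rater's latitude.

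Most of this stands as a limit on the conclusion. It does not remove the contradiction. The blinding statement covers every interviewer, so a change of person between months 4 and 12 does not satisfy it. Scoring training is not blinding. If the row is a mislabel, it still needs correcting, because a site working from the schedule cannot tell which role applies.

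A reader might also infer that the progress notes and communication log unblind the raters, since Table 2 lists all staff for both ("Progress notes All", "Communication log All"). The document does not support that. It does not say that entries record the arm or that interviewers read other people's entries. The Treatment adherence section directs participants with difficulties to the study coordinators, not to the raters. Rules on file access are detail that an article commonly leaves to the full protocol. These two rows are not evidence here.

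**Conclusion.** The contradiction is real and limited. The interviewer-blinding statements and the coordinator roles conflict with one row of Table 3, and the role named in that row also rates the primary outcome. Followed as written at month 4, the row would place arm-specific treatment in raters' hands before the 12-month ADASCog.

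A reader might go further and conclude that raters will learn the arm, or that the claim of blinding is false. That would require Table 3 to override the Treatment adherence section, the Discussion and the Table 2 treatment row, and nothing in the document says it does. The supported conclusion is that the passages disagree and must be reconciled.

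The consequence has no size that can be derived from the protocol. The false-positive rates of 10% to 26% describe an assumed leniency of 0.10 to 0.20 SD. They would apply to any trial of this size with raters who favour the active arm, and are not a property of this one. The correction is worth making because the row touches the only masking of the primary outcome.

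**What to change.** - In Table 3, assign the treatment revision row to the coordinators, in line with the Treatment adherence section, the Discussion and the Table 2 treatment row.
- State that interviewers have no access to a participant's treatment. Where month-4 test results are passed on for treatment modification, interviewers supply them as scores under the participant code and take no part in the revision.
- Reconcile the section on modifications with the Discussion on whether adjustment uses the month-4 tests or programme data only. Which rule applies is for the trial team to decide; the text should state one.

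The cost is one table cell and two sentences. The coordinators already hold the treatment role, so no staff or visits are added, and the sample size and analysis are unaffected.

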**Fig. 1 Fig1:**
[figure not shown]
Standard Protocol Items: Recommendations for Interventional Trials (SPIRIT) Figure. Recommended items to address in a clinical trial protocol and related documents

## Trial status

The RCT trial on the effectiveness of GRADIOR started on 1 September 2016 and will be recruiting participants from 1 September 2017. The end of the trial is foreseen for 1 September 2019.

## Abbreviations

ADASCog: Alzheimer’s Disease Assessment Scale – Cognitive Subscale
BDI-II: Beck Depression Inventory, 2nd edition
CAMCog: Cambridge Cognition Examination
CDR: Clinical Dementia Rating
COM: Combined treatment
dC: Standardised Mean Index difference
dMR: Standardised Mean Change Index
DSM-5: *Diagnostic and Statistical Manual of Mental Disorders*
EQ5D-5 L: EuroQoL 5 dimensions, 5 levels
ETUQ: Everyday Technology Use Questionnaire
GDS: Geriatric Depression Scale
GRA: GRADIOR
IBIP: Centro Ibérico de Investigación en Psicociencias (Iberian Research in Psychosciences Institute)
ICT: Information and communication technology
IESCYL: Instituto de Estudios de Ciencias de la Salud de Castilla y León (Study Institute of Health Sciences of Castile and Leon health system)
IWG: International Working Group
LSNS: Luben Social Network Scale
MCI: Mild cognitive impairment
MMSE: Mini Mental State Examination
PSS: Psychosocial stimulation
PwaMCI: People with amnestic MCI
PwD: People with dementia
QCPR: Quality of Patient-carer Relationship
QoL: Quality of life
RCT: Randomised controlled trial
Sacyl: Health system in Castile and Leon
SE: Standard error
STAI: State-Trait Anxiety Inventory
SUS: System Usability Scale
TAU: Treatment as usual
TMT: Trail-making test
USAL: University of Salamanca
WAIS-III: Wechsler Adult Intelligence Scale, 3rd edition
